# Evaluation of the protective efficacy of a spatial repellent to reduce malaria incidence in children in western Kenya compared to placebo: study protocol for a cluster-randomized double-blinded control trial (the AEGIS program)

**DOI:** 10.1186/s13063-022-06196-x

**Published:** 2022-04-05

**Keywords:** Spatial repellent, Malaria, Transfluthrin, Clinical trial, Kenya

## Abstract

**Background:**

Spatial repellents are widely used for prevention of mosquito bites and evidence is building on their public health value, but their efficacy against malaria incidence has never been evaluated in Africa. To address this knowledge gap, a trial to evaluate the efficacy of Mosquito Shield™, a spatial repellent incorporating transfluthrin, was developed for implementation in Busia County, western Kenya where long-lasting insecticidal net coverage is high and baseline malaria transmission is moderate to high year-round.

**Methods:**

This trial is designed as a cluster-randomized, placebo-controlled, double-blinded clinical trial. Sixty clusters will be randomly assigned in a 1:1 ratio to receive spatial repellent or placebo. A total of 6120 children aged ≥6 months to 10 years of age will be randomly selected from the study clusters, enrolled into an active cohort (baseline, cohort 1, and cohort 2), and sampled monthly to determine time to first infection by smear microscopy. Each cohort following the implementation of the intervention will be split into two groups, one to estimate direct effect of the spatial repellent and the other to estimate degree of diversion of mosquitoes and malaria transmission to unprotected persons. Malaria incidence in each cohort will be estimated and compared (primary indicator) to determine benefit of using a spatial repellent in a high, year-round malaria transmission setting. Mosquitoes will be collected monthly using CDC light traps to determine if there are entomological correlates of spatial repellent efficacy that may be useful for the evaluation of new spatial repellents. Quarterly human landing catches will assess behavioral effects of the intervention.

**Discussion:**

Findings will serve as the first cluster-randomized controlled trial powered to detect spatial repellent efficacy to reduce malaria in sub-Saharan Africa where transmission rates are high, insecticide-treated nets are widely deployed, and mosquitoes are resistant to insecticides. Results will be submitted to the World Health Organization Vector Control Advisory Group for assessment of public health value towards an endorsement to recommend inclusion of spatial repellents in malaria control programs.

**Trial registration:**

ClinicalTrials.govNCT04766879. Registered February 23, 2021.

**Supplementary Information:**

The online version contains supplementary material available at 10.1186/s13063-022-06196-x.

## Administrative information

Note: the numbers in curly brackets in this protocol refer to SPIRIT checklist item numbers. The order of the items has been modified to group similar items (see http://www.equator-network.org/reporting-guidelines/spirit-2013-statement-defining-standard-protocol-items-for-clinical-trials/).

## Introduction

## Background and rationale {6a}

Despite intensive scale up of insecticide-treated nets (ITNs) and effective anti-malarials, malaria remains one of the primary causes of morbidity and mortality in the region [1]. Malaria transmission and burden in areas of western Kenya have been reported to be among the highest in the world. After a period of decline, malaria burden has remained stable over the last few years and may be increasing in some areas. New prevention and control tools are needed to further reduce malaria transmission and accelerate progress towards elimination and eventual eradication [2], which includes addressing the threat of insecticide resistance and outdoor biting vectors [3].

Spatial repellents (SRs) are a promising new vector control paradigm that could add to the existing armamentarium for malaria prevention [4–7], and the World Health Organization (WHO) has recommended methods to evaluate the efficacy of new SR products [8]. SRs are products that contain chemicals that reduce human-vector contact by eliciting a range of behaviors in insect vectors [9], including movement away from chemical stimuli [10], interference with host detection, attraction inhibition, and/or reduced feeding response [11] providing (1) protection against daytime, early-evening biting; (2) protection in enclosed/semi-enclosed and peri-domestic spaces; (3) a range of formulation options to fit context-specific application requirements thereby facilitating health systems strengthening; and (4) increased coverage of vector control over traditional methods. In addition, SR product active ingredients (AIs) have demonstrated increased attraction to oviposition cues [12] that could intervene in the vector life-cycle or enhance combination interventions (i.e., push-pull) [13] and have demonstrated effect on mosquito fecundity [14] and against insecticide-resistant vector species linked to malaria transmission [15]. Currently, the majority of commercial SR products utilize either low concentrations of short-duration United States Environmental Protection Agency (USEPA) [16] registered synthetic pyrethroids (pyrethrin, metofluthrin, and more recently transfluthrin) or botanical-based compounds [7, 17].

Existing malaria vector control guidelines do not recommend the use of SRs for personal protection [18]. However, various SR products have been shown to reduce mosquito biting [19–25] and, in epidemiological studies conducted in Indonesia [26], China [27], and Peru [28] have been shown to reduce pathogen transmission in human populations. In Indonesia, using a transfluthrin-based SR product, Shield with a 2-week duration of protection, a 27.7% reduction in time to first-event and 31.3% in overall infections was demonstrated, but outcomes were not statistically significant due to low incidence in some clusters at baseline, undermining the power to detect a protective effect [26]. Additionally, the study demonstrated a 16.4% and 11.3% reduction in anopheline attack rates indoors and outdoors of households (HHs), respectively. In the Peru trial, the same SR intervention was used, Shield, which significantly reduced arboviral infections by 34.1% with an associated reduction in *Aedes aegypti* abundance and blood-fed capture rates by 28.6% and 12.4%, respectively [28].

The Kenya trial described here will evaluate the efficacy of a next-generation formulation of the SR product used in the Indonesia and Peru trials, Mosquito Shield™, with a duration of protection up to 4 weeks. The choice to use the Mosquito Shield^TM^ product was based on this product containing the same active ingredient and design (i.e., passive emanator) as was used in clinical trials dating back to 2013 which demonstrated impact to reduce malaria and arbovirus infections [28, 29]. Thus, preliminary public health value data exists for this “first-in-kind” prototype for the SR class. The study also been designed to demonstrate whether deployment of SRs will or will not result in increased malaria transmission and disease among geographically proximal non-users.

This evaluation will serve as a proof-of-principle of SR product protective effect for sub-Saharan Africa. Trial results will be submitted to the WHO Vector Control Advisory Group (VCAG) to contribute to the body of evidence regarding the impact of SRs in reducing human malaria infections in settings where underlying transmission rates are high at baseline, ITNs are widely deployed, and/or where mosquito vectors bite outdoors. The outcomes of this study will inform policy recommendations for SRs as a means to further reduce malaria transmission.

### Objectives {7}

The study’s primary objective is to demonstrate and quantify the protective efficacy (PE) of the Mosquito Shield™, a transfluthrin-based SR product, in reducing the incidence of malaria infection in humans.

Secondary objectives will address issues related to the optimization and application of SR products for public health and confirm the range of contexts within which SR PE can be achieved. Secondary objectives are:
To estimate the total number of infections averted due the SR intervention by comparing the number of infections per person per year in intervention and control arms over the 2-year follow-up period;To investigate whether the SR intervention induces diversion of mosquitoes from within intervention areas to locally unprotected individuals thereby having a differential impact on infection incidence among protected and locally unprotected individuals;To measure the impact of the SR intervention on entomological correlates of transmission (e.g., vector densities, mosquito infection, host seeking/biting and parity rates) to set benchmark thresholds and streamline future intervention trials with other SR products by measuring those endpoints correlated to PE.

### Trial design {8}

An outline of the trial design and sample size is summarized in Table 1. This study is a cluster-randomized controlled trial (cRCT) with 30 clusters per treatment arm (SR and placebo), consisting of 4 months of baseline data collection and after baseline, two independent cohorts enrolled (cohort 1 and cohort 2) and each followed for 12 months for a total of a 24-month follow-up with intervention.

**Table 1 Tab1:** Outline of the cluster design and sample size for the SR cRCT in Busia County, Kenya

Cluster design	Baseline cohort	Intervention cohorts		
	4-month follow-up (*n* = 2040)	Time of intervention deployment	12-month follow-up (cohort 1) (*n* = 2040)	12-month follow-up (cohort 2) (*n* = 2040)
**Core area** 60 clusters total	20 subjects per cluster 1200 subjects total	Year 1	SR (30 clusters), Placebo (30 clusters) 14 subjects per cluster 840 subjects total	n/a
		Year 2	n/a	SR (30 clusters), Placebo (30 clusters) 14 subjects per cluster 840 subjects total
**Buffer zone** 60 clusters total	14 subjects per cluster 840 subjects total	Year 1	SR (30 clusters), Placebo (30 clusters) 20 subjects per cluster 1200 subjects total	n/a
		Year 2	n/a	SR (30 clusters), Placebo (30 clusters) 20 subjects per cluster 1200 subjects total

For the evaluation of the primary epidemiological objective (PE), a total of 28 subjects (HHs) will be recruited from each core area of a cluster or equivalently 14 subjects (HHs) per cohort per cluster (factoring in a 35% loss-to-follow-up (LTFU) rate). For the evaluation of the secondary epidemiological objective on SR diversionary effect, a total of 40 subjects (HHs) or equivalently 20 subjects (HHs) per cohort per cluster will be recruited from each buffer zone (factoring in a 35% LTFU rate). At least one child aged ≥ 6 months old to 9 years and 11 months old from each HH will be recruited for biweekly (every 2 weeks) malaria check-ups during the follow-up period with intervention.

Twenty clusters (10 SR, 10 placebo) will be randomly selected to estimate the impact of the SR on entomological measures of malaria transmission. These clusters will remain fixed throughout the study. Within each of the 20 clusters, light trap collections will be conducted monthly in 10 randomly selected HHs within the core area of each sentinel cluster to assess the impact of SRs on the density of *Anopheles* mosquitoes indoors. On the same night, light trap collections will also be conducted in 15 randomly selected HHs in the buffer zone of the same cluster to estimate the diversionary effect of the SR. Human landing catches (HLC) will be performed indoors and outdoors of 48 HHs in a subset of 12 (6 SR intervention, 6 placebo) of the 20 clusters selected for entomology evaluation to determine the effect of SR on the host seeking behavior of mosquitoes. The 12 clusters will remain fixed throughout the study. Sampling will be performed in four houses (randomly selected) in each cluster for two nights once every quarter (3 months). The same houses will be sampled each quarter.

Each cluster will consist of a core area, which corresponds to an existing village, and a buffer zone which includes HHs outside but within 300–500 m of the core area (Fig. 1). Based on studies evaluating mass effect of ITNs [30], endpoints measured in the buffer zone in our trial will be used to quantify induced diversion by the SR intervention on mosquitoes from within cluster core areas to locally unprotected individuals in the buffer zones thereby potentially having a differential impact on malaria infection incidence among protected and locally unprotected individuals.

**Fig. 1 Fig1:**
[figure not shown]
Location of 60 study clusters in Teso North and Teso South Districts, Busia County, western Kenya. Each cluster consists of a core area (discrete village) and a buffer zone extending 300–500 m outside the core area in which diversionary effects of the SR intervention on epidemiological and entomological endpoints will be measured

## Methods: participants, interventions, and outcomes

### Study setting {9}

The study will be conducted in Busia County, which is located on the border with Uganda, approximately 100 km northwest of Kisumu City. Busia County has a population of 743,946 which is made up of primarily the Luo, Luhya, and Teso ethnic groups. The population of the area identified for this study is predominantly of the Teso ethnic group. The population lives in scattered homesteads and survives primarily as subsistence farmers. Malaria transmission is high and perennial with seasonal peaks in June–July and October–November which follow rainfall patterns. The long rains occur from late March to early June and the short rains occur around October through November. The primary mosquito vectors observed in the area include *An. gambiae s.s.*, *An. arabiensis*, and *An. funestus* [31].

In the 2015 Malaria Indicator Survey, malaria prevalence among children aged 6 months to 14 years in the Lake endemic region was 42.4% by rapid diagnostic test (RDT) and 26.7% by microscopy [32]. A study conducted in Busia County in 2013–2014 found the incidence of malaria infections ranged between 2.5 and 4.1 per person per year [33]. ITN coverage is high, with 88.2% of HHs owning at least one ITN and 68.4% of persons reporting sleeping under a net the previous night [32]. Due to the continued high burden of malaria despite high coverage of ITNs and the presence of KEMRI/CDC malaria research in the region, this site was selected to evaluate the efficacy of the Mosquito Shield™ intervention.

### Eligibility criteria {10}

The inclusion and exclusion criteria are listed in Table 2. All children aged ≥ 6 months to 10 years of age who report sleeping in selected study clusters > 90% of the nights of each month and do not have any plans to travel outside the study area (for more than 5 consecutive weeks) will be eligible for inclusion in the study. Children aged 5 to < 10 years have the highest malaria prevalence in this area, and so it was deemed important to include them to estimate the potential benefit of SR on this population. This will allow us to assess the impact on different age groups and infer the added benefit of the Mosquito Shield™ on top of long-lasting insecticidal nets (LLINs), for which coverage is lower among older aged children. Children who have a measured hemoglobin at baseline of ≤5 mg/dL or < 6 mg/dL with signs of clinical decompensation will be excluded from the study. Persons who are participating in another clinical trial investigating a drug, vaccine, medical device, or procedure will also be excluded from the study. The written consent of the parent or legal guardian of each child is required for inclusion in the study.

**Table 2 Tab2:** Inclusion and exclusion study criteria

Inclusion criteria	Exclusion criteria
Children aged 6 months to < 10 years	Children < 6 months or ≥ 10 years
Hb > 5 mg/dl	Hb ≤ 5 mg/dL, or Hb < 6 mg/dL with signs of clinical decompensation
Sleeps in cluster > 90% of nights during any given month	Sleeps in cluster < 90% of nights during any given month
No plans for extended travel (> 1 month) outside of home during study	Plans for extended travel (> 1 month) outside of home during study
Not participating in another clinical trial investigating a vaccine, drug, medical device, or a medical procedure during the trial	Participating or planned participation in another clinical trial investigating a vaccine, drug, medical device, or a medical procedure during the trial
Provision of informed consent form (ICF) signed by the parent(s) or guardian	No provision of ICF signed by the parent(s) or guardian
Children not on regular malaria prophylaxis***	Children on regular malaria prophylaxis***
Willingness to take Artemether-Lumefantrine (AL) and no history of hypersensitivity to AL	Unwillingness or refusal to take AL and history of AL hypersensitivity

***** Malaria prophylaxis medicines: Mefloquine, Atavaquone/Proguanil (Malarone), Doxycycline, Sulfadoxine-Pyrimethamine (Fansidar), Amodiaquine, and Co-trimoxazole (Septrin)

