#### Enrolment of the cohort

Cohorts of children aged ≥ 6 months to 9 years 11 months will be enrolled from randomly selected compounds using a master list generated during baseline mapping to achieve the desired sample size (see “Recruitment {15}”). HHs within each cluster will be identified by simple random sampling using a statistical software package such as SAS, STATA, or R. Selected HHs will be visited and all eligible children in the HH invited to participate in the study. The children will be enumerated on a tablet and a randomization program run to pick one who will be invited to participate in the study. The study will be explained and consent obtained from the child’s parent/guardian before enrolling the child in the study.

At enrolment, the age and sex of the child will be recorded and the parent/guardian will be asked about the use of ITNs and anti-malarial drugs. A fingerstick blood sample will be taken for a malaria RDT, a blood smear, and a measurement of hemoglobin. At this time, cohort participants will be presumptively cleared of parasites with a treatment dose of AL unless they have recently been treated (within the last 2 weeks) in which case, their microscopy results will be fast-tracked to confirm clearance and if not cleared, another dose of AL will be given. Children will be treated according to Rapid Diagnostic Test (RDT) result throughout the follow-up period unless the microscopy result is positive following a negative RDT or where an RDT was not done.

All enrolled children will be provided a LLIN. This will allow us to measure the added benefit of SR product above that provided by current WHO recommended malaria preventive measures. In addition, children enrolled into each baseline, cohort 1, and cohort 2 will be provided a treatment dose of AL free of charge to clear any prepatent or patent malaria parasites.

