## Trial status

Under protocol version 7 from November 20, 2020, recruitment for the baseline cohort began March 1, 2021, and final subject enrolment was completed April 2, 2021.

The study has currently completed the baseline phase (as of July 31, 2021), whereby participants have been recruited, screened, and enrolled and followed up without intervention for 4 months. Baseline data analyses are ongoing to verify underlying assumptions of malaria incidence, coefficient of variation, and loss to follow-up. Recruitment, screening, and enrolment of subjects for follow-up with intervention is scheduled to commence in August 2021.

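### The haemoglobin entry limits are printed in mg/dL throughout, 1000 times too low, so as written the criterion excludes no child

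*Protocol article*

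**What the plan says.** In the protocol article, the section Eligibility criteria {10} sets a haemoglobin limit for entry. The running text says that children with a "measured hemoglobin at baseline of ≤5 mg/dL or < 6 mg/dL with signs of clinical decompensation will be excluded from the study". Table 2, in the same section, gives the exclusion as "Hb ≤ 5 mg/dL, or Hb < 6 mg/dL with signs of clinical decompensation", and its inclusion column gives the matching lower limit of more than 5, also in milligrams per decilitre.

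The section Enrolment of the cohort describes how the value is obtained: "A fingerstick blood sample will be taken for a malaria RDT, a blood smear, and a measurement of hemoglobin". It gives no unit. No other section states the limit again or gives it in g/dL.

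**The concern.** Haemoglobin limits of 5 and 6 make sense in g/dL, where they mark severe anaemia. In mg/dL they lie far below any value a living child could have. The link to clinical decompensation shows that the rule is meant to keep severely anaemic children out of the cohorts. With the printed unit it cannot do so.

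The rule matters because it is the only laboratory value in Table 2. The other criteria concern age, nights slept in the cluster, travel, participation in other trials, consent, malaria prophylaxis, and willingness and ability to take artemether-lumefantrine. The children are as young as 6 months and live in an area of high, year-round transmission.

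The error could also spread. The section Data quality control and quality assurance says that the tablet forms and the database will carry rules that include numeric limits. If the printed limit were copied into such a rule and compared with values held in mg/dL, every child would pass without a warning. If the device reports in g/dL and only the numerals were copied, the rule would work as intended. The article does not show which unit the forms use.

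**Working it through.** **Inputs**, all from Eligibility criteria {10} and Table 2 of the protocol article:

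| Place | Limits stated | Unit | Statements |
|---|---|---|---|
| Running text | at most 5; below 6 with decompensation | mg/dL | 2 |
| Table 2, inclusion | above 5 | mg/dl | 1 |
| Table 2, exclusion | at most 5; below 6 with decompensation | mg/dL | 2 |

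Count: 2 + 1 + 2 = 5 statements, none in g/dL.

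**Conversion.** 1 g/dL = 1000 mg/dL.

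- 5 mg/dL = 5/1000 = 0.005 g/dL
- 6 mg/dL = 6/1000 = 0.006 g/dL
- Intended over written: 5/0.005 = 6/0.006 = 1000

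**Applying the rule as written.** A child is excluded at 5 mg/dL or less, or below 6 mg/dL with decompensation.

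| Child's haemoglobin (g/dL) | In mg/dL | Excluded as written? | Excluded if the unit is g/dL? |
|---|---|---|---|
| 3 | 3000 | No | Yes |
| 5 | 5000 | No | Yes |
| 6 | 6000 | No | No |
| 8 | 8000 | No | No |
| 11 | 11000 | No | No |
| 13 | 13000 | No | No |

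Under the g/dL reading, a child above 5 and below 6 g/dL would be excluded only with signs of decompensation.

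**Distance from any attainable value.** The article gives no lowest survivable haemoglobin. Taking 1 to 2 g/dL as an assumption, that is 1000 to 2000 mg/dL. The ratio to the 5 mg/dL limit is 1000/5 = 200 to 2000/5 = 400. The ratio to the 6 mg/dL limit is 1000/6 ≈ 167 to 2000/6 ≈ 333. The conclusion does not depend on where in that range the true value lies.

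**The case against.** The strongest reply is that no clinician would read the limit literally. The intent is plain from the numerals and from the mention of decompensation, and staff using a device that reads in g/dL would most likely apply 5 and 6 g/dL. The five statements repeat one slip. Other safeguards exist: presumptive antimalarial treatment at enrolment, monthly clinic visits, data checks, external monitoring, and the right of staff to end a child's participation on clinical grounds. The article also condenses a fuller protocol (version 7), which may carry the right unit.

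Most of this stands, and it is why the point is minor. Haemoglobin is not an outcome, is not among the baseline characteristics listed for summary, and does not enter the sample size, the hypotheses or the interim boundaries. There is no evidence that any child was wrongly enrolled.

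It does not make the printed limit correct. The article states a threshold, states it wrongly every time, and gives the reader nothing to correct it from. The same wrong unit in running text and in both table columns is unlikely to come from faulty text extraction. The data checks help only if they were set up in the right unit, which the article does not show.

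**Conclusion.** The concern holds. All five statements of the haemoglobin limit carry the wrong unit, and the written limits are 1/1000 of the evident intent. Taken literally, the criterion excludes no child. This is a unit error, probably typographical, and not a wrong calculation.

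Severity is minor. Type I error, power, sample size and the primary analysis are unaffected, and the practical harm is probably small. The conclusion rests on two things outside the text: that 5 and 6 g/dL were meant, and that no living child has haemoglobin near 0.005 g/dL. Neither is in serious doubt. The article does not say how many children fall at or below the intended limits, so no number wrongly enrolled can be given. Whether the approved protocol or the screening form carries the same error cannot be judged from the article.

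**What to change.** 1. Check the approved protocol for the intended unit, then change mg/dL to g/dL in all five places: two in the running text, one in the inclusion column and two in the exclusion column of Table 2. The numerals 5 and 6 stay.
2. Before any enrolment still to come, confirm that the screening form and any tablet rule use the unit the haemoglobin device reports. The Trial status section says: "Recruitment, screening, and enrolment of subjects for follow-up with intervention is scheduled to commence in August 2021". The article appeared in April 2022, so if that schedule held, cohort 1 was already enrolled by publication and only cohort 2, due from August 2022, could be checked in advance.
3. For cohorts already enrolled, including the completed baseline cohort, a check of the unit on the completed screening forms is enough.

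The cost is an erratum or wording amendment and a check of the forms. No participant, procedure or analysis is added.
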